## Abstract

**Background:**

Pneumonia is the leading infectious cause of death worldwide among children below 5 years of age. Clinical trials are conducted to determine optimal treatment; however, these trials often exclude children with comorbidities and severe illness.

**Conclusions:**

Given the paucity of data from Africa, African-based research is necessary to establish optimal management of childhood pneumonia in malaria-endemic settings in the region. An expanded evidence base that includes children with pneumonia and other comorbidities, who are at high risk for mortality or have other complications and are therefore typically excluded from childhood pneumonia clinical trials, can contribute to future iterations of the World Health Organization Integrated Management of Childhood Illness guidelines.

**Methods:**

The study enrolled 1000 children with pneumonia presenting to the outpatient departments of Kamuzu Central or Bwaila District Hospitals in Lilongwe, Malawi, who were excluded from concurrent randomized controlled clinical trials investigating fast breathing and chest indrawing pneumonia and who met the inclusion criteria for this prospective observational study. Each child received standard care for their illnesses per Malawian guidelines and hospital protocol and was prospectively followed up with scheduled study visits on days 1, 2 (if hospitalized), 6, 14 (in person), and 30 (by phone). Our primary objectives are to describe the clinical outcomes of children who meet the inclusion criteria for this study and to investigate whether the percentages of children cured at day 14 among those with either fast breathing or chest indrawing pneumonia and comorbidities such as severe malaria, anemia, severe acute malnutrition, or HIV are lower than those in children without these comorbidities in the standard care groups in concurrent clinical trials. This study was approved by the Western Institutional Review Board, Malawi College of Medicine Research and Ethics Committee, and the Malawi Pharmacy, Medicines and Poisons Board.

**Objective:**

This prospective observational study aimed to assess the clinical outcomes of children aged 2-59 months with both pneumonia and other comorbidities in a malaria-endemic region of Malawi.

**Results:**

The Innovative Treatments in Pneumonia project was funded by the Bill and Melinda Gates Foundation (OPP1105080) in April 2014. Enrollment in this study began in 2016, and the primary results are expected in 2019.

**International Registered Report Identifier (IRRID):**

DERR1-10.2196/13377

## Introduction

Pneumonia is the leading infectious cause of childhood mortality worldwide. As part of the Innovative Treatments in Pneumonia (ITIP) project conducted in Lilongwe, Malawi, two randomized controlled clinical trials are evaluating the optimal duration of treatment with amoxicillin for fast breathing (ITIP1) and chest indrawing (ITIP2) childhood pneumonia [1]. Clinical trials evaluating the treatment for pneumonia often exclude children with comorbidities who are at high risk for mortality or have other complications. Pneumonia with comorbidities is common, and many factors determine whether contact with an etiologic agent will result in a severe episode of pneumonia and whether the episode will be fatal [2-6]. These factors can be related to the child (eg, age, sex, and underlying diseases), disease (eg, type of infection), environment, family and its socioeconomic status, or health system and type of care [7]. A systematic review and meta-analysis of risk factors for mortality from acute lower respiratory infections in children under the age of 5 years in low- and middle-income countries found that chronic underlying diseases (odds ratio [OR] 4.76, 95% CI 3.27-6.93), HIV/AIDS (OR 4.68, 95% CI 3.72-5.90), and severe malnutrition (OR 4.27, 95% CI 3.47-5.25) were associated with mortality due to acute lower respiratory infections [7]. In an effort to generate data on pneumonia treatment outcomes among high-risk African children after introduction of the *Haemophilus influenzae* type b and *Streptococcus pneumoniae* conjugate vaccines and to better interpret the results of the concurrent clinical trials, a prospective observational study (ITIP3) to assess the clinical outcomes of children aged 2-59 months with both pneumonia and other comorbidities was conducted. Given the paucity of data from Africa, African-based research is necessary to establish optimal treatment regimens for childhood pneumonia in the region.

## Methods

### Ethical Approval

The study was approved by the Western Institutional Review Board in the state of Washington, USA; the Malawi College of Medicine Research and Ethics Committee, Blantyre, Malawi; and the Malawi Pharmacy, Medicines and Poisons Board. Written informed consent was obtained by trained study staff from all eligible children’s caregivers prior to enrollment.

### Study Design and Settings

The primary objective of this prospective, observational study is to determine the clinical outcomes of children aged 2-59 months with pneumonia and other comorbidities in Lilongwe, Malawi, who were excluded from ITIP1 and ITIP2 pneumonia treatment clinical trials and meet the inclusion criteria for ITIP3. We will also investigate whether the percentages of children cured on day 14 from diagnosis among those with either fast breathing or chest indrawing pneumonia and comorbidities such as severe malaria, anemia, severe acute malnutrition, or HIV are lower than those without these comorbidities in the standard care groups in the concurrent clinical trials. The primary aim of the ITIP1 and ITIP2 clinical trials is to provide evidence for the optimal duration of treatment of children with fast breathing or chest indrawing childhood pneumonia (but without other major comorbidities) with amoxicillin dispersible tablets. These two randomized controlled clinical trials are conducted with immunocompetent children aged 2-59 months residing in a malaria-endemic region of Malawi. Children enrolled in the clinical trials are followed for 14 days, with ITIP1 follow-up assessments conducted on days 2, 3, 4, and 14 and ITIP2 follow-up assessments conducted on days 2, 4, 6, and 14. The prospective observational study ITIP3 enrolls children with pneumonia who are excluded from the two clinical trials because of other comorbidities in an effort to provide additional valuable evidence on standard care and outcomes for children with pneumonia in Malawi who are most at risk for mortality or have other complications. An observational design was chosen to follow the clinical outcomes of high-risk children with pneumonia who are typically excluded from clinical trials. This study is conducted at the outpatient and inpatient departments of Kamuzu Central Hospital (KCH) and the outpatient department of Bwaila District Hospital (BDH) in Lilongwe, Malawi (Figure 1). The 750-bed government facility KCH is the primary referral hospital for the central region of Malawi, serving a population of approximately 5 million people. BDH is the district hospital for Lilongwe with no inpatient facilities for children. Children requiring inpatient care are referred to KCH.

**Figure 1 figure1:**
[figure not shown]
Map of the study area in Lilongwe, Malawi. KCH: Kamuzu; BDH: Bwaila District Hospital.

### Study Participants

Children aged 2-59 months with cough or difficulty breathing were recruited by trained hospital staff during routine intake and screening procedures in the hospitals’ outpatient departments and referred to the study staff for information on the study, written informed consent, and additional screening to determine enrollment eligibility (Figure 2). Screening procedures included assigning a participant an identification number; collecting demographic and contact information and medical history; and assessing eligibility criteria with a targeted physical examination, malaria rapid diagnostic testing, HIV rapid antibody testing, hemoglobin testing, and bronchodilator response testing (if wheezing).

Caregivers of eligible children meeting the case definition (Textbox 1) of fast breathing or chest indrawing pneumonia, who do not meet the eligibility criteria for ITIP1 and ITP2 clinical trials and meet the eligibility criteria for ITIP3 (Textbox 2) were invited to participate by providing written informed consent for enrollment. Final eligibility determination for enrollment depended on the results of the medical history, clinical examination, laboratory testing, appropriate understanding of the study (comprehension assessment checklist), and completion of the enrollment consent process.

Clinical cure was defined as (1) the absence of fast breathing, chest indrawing, severe respiratory distress, hypoxemia, World Health Organization (WHO) Integrated Management of Childhood Illness (IMCI) general danger signs, and fever; (2) cure from pneumonia but failure to complete the initial antibiotic treatment regimen; and (3) cure from pneumonia and completion of the initial antibiotic treatment regimen. In contrast, those who showed a deterioration in their condition or were stable (not improving or deteriorating, prognosis unclear) were not considered to be clinically cured.

**Figure 2 figure2:**
[figure not shown]
Schedule of enrollment and follow-up assessment. ITIP1: Innovative Treatments in Pneumonia 1, randomized controlled clinical trial evaluating the optimal duration of treatment with amoxicillin for fast breathing pneumonia;ITIP2: Innovative Treatments in Pneumonia 2, randomized controlled clinical trial evaluating the optimal duration of treatment with amoxicillin for chest indrawing pneumonia; ITIP3: Innovative Treatments in Pneumonia 3, prospective observational study.

Study definitions.Study definitionsFast breathing pneumonia: Cough less than 14 days or difficulty breathing AND fast breathing for ageChest indrawing pneumonia: Cough less than 14 days or difficulty breathing AND visible indrawing of the chest wall with or without fast breathing for ageFast breathing for age: Respiratory rate >50 breaths per minute (for children aged 2 to <12 months of age) or >40 breaths per minute (for children aged >12 months of age)Very fast breathing for age: >70 breaths per minute (for children aged 2 to <12 months of age) or >60 breaths per minute (for children aged >12 months of age)Severe respiratory distress: Grunting, nasal flaring, and/or head noddingHypoxemia: Arterial oxyhemoglobin saturation < 90% in room air, as assessed noninvasively by a pulse oximeterWorld Health Organization Integrated Management of Childhood Illness general danger signs: Lethargy or unconsciousness, convulsions, vomiting everything, and inability to drink or breastfeedSevere acute malnutrition: Weight for height/length < –3 SD, mid-upper arm circumference < 11.5 cm, or peripheral edemaSevere malaria: Positive malaria rapid diagnostic test with any World Health Organization Integrated Management of Childhood Illness general danger sign, stiff neck, abnormal bleeding, clinical jaundice, or hemoglobinuriaHIV exposure: Children <24 months of age with an HIV-infected motherSerious adverse event: Adverse event thatResults in deathIs life threateningRequires inpatient hospitalization or prolongation of existing hospitalizationResults in persistent or significant disability/incapacityIs a medical event, based on appropriate medical judgment, that may jeopardize the health of the participating child or require medical or surgical intervention to prevent one of the outcomes listed

Eligibility criteria.Inclusion criteria:2-59 months of ageCough < 14 days or difficulty breathingExcluded from enrollment in ITIP1 and ITIP2 clinical trials due to the presence of any of the following:Severe respiratory distressHypoxemiaHemoglobin level < 8.0 g/dL, if positive malaria rapid diagnostic testSevere acute malnutritionSevere malariaHIV seropositivity or HIV exposureAbility and willingness of child’s caregiver to provide informed consent and to be available for follow-up for the planned duration of the study, including accepting a home visit if he/she fails to return for a scheduled study follow-up visitExclusion criteria:Stridor when calmPossible tuberculosis (coughing for more than 14 days)Hemoglobin level < 8.0 g/dL, if negative malaria rapid diagnostic testKnown allergy to penicillin or amoxicillinReceipt of an antibiotic treatment in the 48 hours prior to the studyLiving outside the study areaAny medical or psychosocial condition or circumstance that, in the opinion of the investigators, would interfere with the conduct of the study or for which study participation might jeopardize the child’s healthParticipation in a clinical study of an investigational product within 12 weeks prior to enrollment or planning to begin participation during this studyPrior participation in ITIP1, ITIP2, or ITIP3 during a previous pneumonia diagnosis

### Study Procedures

All study procedures are conducted according to the protocol provided in Multimedia Appendix 1 (version 4.0; May 26, 2017). On day 1, after study screening was complete and enrollment informed consent was obtained, the study staff performed the following procedures for enrollment: conducting physical examination, obtaining vaccination history, and collecting additional sociodemographic information. Recruitment, screening, and enrollment occur at the outpatient departments of KCH or BDH, with BDH enrollees transferred to KCH for continued evaluation, observation, and admission, if needed. Hospital observation or admission and follow-up occur solely at KCH.

Each enrolled child receives standard care for their illnesses per Malawian guidelines and KCH protocol and is prospectively followed up by the study staff with scheduled study visits on days 1, 2 (if hospitalized), 6, 14 (in person), and 30 (by phone). All visits occur on the calendar day on which they are initially scheduled or within 24 hours, with the exception of the day 14 visit and the day 30 phone call. The day 14 visit can occur either 2 days before or after day 14, and the day 30 phone call can occur either 2 days before or 14 days after day 30 and still be considered completed within the visit windows. During follow-up visits, the study staff review participants’ medical history since the last study visit and perform a physical examination. In case of a no-show at the scheduled follow-up visits, children are followed up with home visits by the study staff. If a phone call on day 30 is not possible due to no phone in the home, the study staff conducts a home visit to obtain the day 30 outcome information.

### Sample Size

The primary objectives of ITIP3 are to describe the clinical outcomes of children who meet the inclusion criteria for ITIP3 and to investigate whether the percentages of children cured on day 14 among those with either fast breathing or chest indrawing pneumonia and comorbidities such as severe malaria, anemia, severe acute malnutrition, or HIV are lower than those without these comorbidities in the standard of care groups in the concurrent clinical trials. For hypothesis testing, we focused on four high-frequency and high-mortality comorbidities (ie, severe malaria, anemia, severe acute malnutrition, and HIV infection or exposure) within ITIP3. We estimate that the study can enroll 1000 children during the time it is concurrently conducted with the ITIP1 and ITIP2 clinical trials, and we estimate the effect sizes for the primary outcome comparisons for which we have 80% power. We also assume that 1000 children can be enrolled in each of the standard care groups in ITIP1 and ITIP2. With available data from KCH and Malawi, we estimate the prevalence of severe pneumonia to be 10%-24%, severe malaria to be 15%-20%, severe acute malnutrition to be 4%-7%, and HIV seropositivity to be 5%-10%. Based on the estimated treatment failure rates for ITIP1 and ITIP2, we conservatively estimate that clinical cure will be observed in 90%-95% of children in ITIP1 and 85%-90% in ITIP2. We estimate the effect sizes we would be able to see for various comparisons between ITIP3 and ITIP1 or ITIP2, along with different estimated prevalence rates (Table 1). For example, comparing the clinical cure among children with HIV infection or exposure in ITIP3 and those in the standard of care group in ITIP2, if the prevalence of HIV infection or exposure is 10% in ITIP3, we will have 80% power to detect an absolute difference in proportions of 9.9% if at least 90% of the children in ITIP2 are cured and 80.1% of the children with HIV infection or exposure in ITIP3 are cured. Note that the absolute observable difference is largest for severe acute malnutrition, as that outcome is expected to have the lowest prevalence among the outcomes of interest. Nonetheless, we considered all the estimated effect sizes to be clinically relevant.

**Table 1 table1:** Observable effect sizes for comparisons of Innovative Treatments in Pneumonia (ITIP) 3^a^ with ITIP1^b^ or ITIP2^c,d^. N (ITIP1 or ITIP2) = 1000.

Exposure of interest, prevalence of exposure (ITIP3), and N (ITIP3)^e^			Absolute observable difference, %	Prevalence of clinical cure (ITIP1 or ITIP2), %	Prevalence of clinical cure (ITIP3), %
**Severe malaria**						
	**20%**					
		200	5.5	95	89.5
		200	7.2	90	82.8
		200	8.3	85	76.7
	**15%**					
		150	6.3	95	88.7
		150	8.1	90	81.9
		150	9.4	85	75.6
**Anemia**						
	**10%**					
		100	7.6	95	87.4
		100	9.9	90	80.1
		100	11.%	85	73.6
	**7.5%**					
		75	8.8	95	86.2
		75	11.3	90	78.7
		75	13.1	85	72.0
**HIV infection or exposure**						
	**10%**					
		100	7.6	95	87.4
		100	9.9	90	80.1
		100	11.4	85	73.6
	**5%**					
		50	10.9	95	84.1
		50	13.9	90	81.3
		50	15.9	85	69.1

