**Severe acute malnutrition**						
	**7%**					
		70	9.1	95	85.9
		70	11.7	90	78.3
		70	13.5	85	71.5
	**4%**					
		40	12.2	95	82.8
		40	15.6	90	74.4
		40	17.8	85	67.2

^a^Prospective observational study.

^b^Randomized controlled clinical trial evaluating the optimal duration of treatment with amoxicillin for fast breathing pneumonia.

^c^Alpha value set to 5% and power set to 80%.

^d^Randomized controlled clinical trial evaluating the optimal duration of treatment with amoxicillin for chest indrawing pneumonia.

^e^Assuming similar values for fast breathing pneumonia and chest indrawing pneumonia to be able to compare the ITIP1 and ITIP2 cohorts.

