### Statistical Analysis

Generalized linear models with robust standard error will be used to compare the percentages (absolute risk differences) of children who are clinically cured by day 14 among ITIP3 children who have severe malaria (or are anemic or present with severe acute malnutrition, or are HIV positive or exposed) and children in the standard care groups in ITIP1 or ITIP2. Two-sided tests will be performed, with an alpha value of 0.05. No adjustments will be made for multiple comparisons because of the observational and exploratory nature of this study. If loss to follow-up is higher than 5%, multiple imputations will be considered for sensitivity analyses. The imputations will be performed separately for each cohort using multiple (n=20) hot deck imputations and the child’s age and gender and educational status of the caregiver. Multiple imputation estimates will be combined using the approach by Rubin [8]. Similar linear or generalized linear models will be used for secondary outcome analyses. Where appropriate, we will adjust for gender, age, weight, mid-upper arm circumference, HIV status, malaria, and vaccination status.

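### Table 1, HIV infection or exposure at 5% prevalence: the ITIP3 cure percentage against a 90% comparator is printed as 81.3, but the row's own difference of 13.9 gives 76.1

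*Protocol article*

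**What the plan says.** The Sample Size section takes the number of children as given and works out what can be detected: "We estimate that the study can enroll 1000 children", and "we estimate the effect sizes for the primary outcome comparisons for which we have 80% power". For the comparator arms, "We also assume that 1000 children can be enrolled in each of the standard care groups in ITIP1 and ITIP2". The lower HIV scenario uses the bottom of the stated range, "HIV seropositivity to be 5%-10" per cent, which gives 50 of 1000 ITIP3 children.

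The section's worked example shows how to read Table 1. With 100 children with HIV infection or exposure, "we will have 80% power to detect an absolute difference in proportions of 9.9% if at least 90% of the children in ITIP2 are cured"; the matching ITIP3 cure percentage is given as 80.1. The last column is therefore the comparator percentage minus the detectable difference (90 − 9.9 = 80.1).

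Footnote c to the table gives the settings: "Alpha value set to 5% and power set to 80" per cent. The Statistical Analysis section adds the sidedness: "Two-sided tests will be performed, with an alpha value of 0.05".

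The row at issue is in the HIV infection or exposure block, 5% prevalence, 90% comparator: "50 13.9 90 81.3".

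**The concern.** The row contradicts itself: a difference of 13.9 points below 90% cannot end at 81.3%. The printed value also breaks the order of the table, because a smaller group needs a larger difference, yet 81.3% lies closer to 90% than the 80.1% listed for twice as many children.

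HIV infection or exposure is one of the four comorbidities chosen for hypothesis testing, and day-14 cure is the primary endpoint. The 90% comparator is the one value common to the ranges assumed for ITIP1 (90%-95%) and ITIP2 (85%-90%), so the row serves both comparisons. The Sample Size section goes on to judge all the listed effect sizes clinically relevant. A reader who makes that judgement from the last column would weigh a deficit of 8.7 points where the plan's own calculation gives 13.9. The slip is in the favourable direction.

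**Working it through.** **Inputs.** Comparator group n0 = 1000 (Sample Size). ITIP3 subgroup n1 = 50, being 5% of 1000 (Sample Size, Table 1). Comparator cure p0 = 0.90 (Table 1). Alpha 0.05 and power 80% (footnote c), two-sided (Statistical Analysis).

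**1. The subtraction rule.** For the two other rows with n = 50, 95 − 10.9 = 84.1 and 85 − 15.9 = 69.1, both as printed. For the row at issue, 90 − 13.9 = 76.1, but 81.3 is printed. The gap is 81.3 − 76.1 = 5.2 points. Table 1 has 24 rows, covering 21 distinct settings because anemia at 10% and HIV at 10% coincide. The only other row that departs from the rule is anemia, n = 75, 85% comparator, by 0.1 point (72.0 against 71.9). That is rounding, since the computed difference is 13.05 and the cure percentage 71.95.

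**2. Which of the two figures is wrong.** The article does not name the formula behind the table. The pooled-variance normal approximation for two proportions was tried:

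power = Φ[(p0 − p1 − 1.96 × SE0) / SE1]

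where SE0 = √[p̄(1 − p̄)(1/n0 + 1/n1)], SE1 = √[p0(1 − p0)/n0 + p1(1 − p1)/n1], and p̄ is the weighted mean of p0 and p1. Solved for 80% power, it reproduces the printed difference in all 21 settings to within about 0.05 point, with the incomplete anemia entry (11.%) read as 11.4, as in the identical HIV row. For 50 against 1000 at 90% it gives 13.90. So 13.9 is right and 81.3 is the wrong cell.

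**3. Power at the two cure percentages, 50 against 1000.**

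- At 76.1%: p̄ = (900 + 38.05)/1050 = 0.8934, SE0 = 0.0447, SE1 = 0.0611. Then (0.139 − 1.96 × 0.0447)/0.0611 = 0.84, and the power is 80.0%.
- At 81.3%: p̄ = (900 + 40.65)/1050 = 0.8959, SE0 = 0.0443, SE1 = 0.0560. Then (0.087 − 1.96 × 0.0443)/0.0560 ≈ 0.00, and the power is 50.2%.

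**4. Could another method give 81.3?** Power at 81.3% under alternatives: one-sided pooled 60.0%, continuity-corrected 42.7%, arcsine 41.0%, unpooled variance 34.3%. A simulation of the pooled test gives 49.0%. None is near 80%. On the pooled method, about 131 ITIP3 children, not 50, would be needed for 80% power at 81.3%.

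**5. Order within the table.** At the 90% comparator, the printed ITIP3 cure percentages are:

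| n (ITIP3) | 100 | 75 | 70 | 50 | 40 |
|---|---|---|---|---|---|
| printed | 80.1 | 78.7 | 78.3 | 81.3 | 74.4 |

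The value for n = 50 must lie between 78.3 and 74.4. The corrected 76.1 does; 81.3 does not.

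**The case against.** The strongest reply is that this is a misprint in a derived column. Table 1 reports observable effect sizes, and for this row the effect size, 13.9, is correct and stands two columns to the left of the error. The worked example and the adjacent rows make the slip visible. The size of ITIP3 came from what could be enrolled, and no sample size, stopping rule or analysis uses the cell. All of that stands and limits the consequence. It does not make the cell right: the row gives two incompatible answers, and nothing else in the article says which one holds.

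A second reply is that the 50% power belongs to the pooled test, whereas the planned analysis is a generalized linear model with robust standard errors, which is closer to an unpooled test. That is fair, so the figure should always carry its method. On the unpooled calculation the power at 81.3% is lower still, about 34%.

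A reader might go further and infer that a null HIV result would be taken to rule out a fall from 90% to 81.3%. The documents do not support this. The Statistical Analysis section plans estimates of absolute risk differences and calls the study exploratory, and nothing ties interpretation to this planning cell. Nor does the finding show that the HIV comparison was planned at 50% power. The calculation was solved for the 13.9-point difference, and at that difference the table's method gives 80%.

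**Conclusion.** The printed 81.3 is wrong and should be 76.1, an overstatement of 5.2 points. Taken at face value it implies a detectable difference of 8.7 points, against the 9.9 points listed for 100 children. Power there would be about 50% on the table's pooled two-sided method, or about 34% unpooled, instead of 80%.

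The subtraction needs no assumption beyond the rule shown by the worked example. That 13.9 is the correct member of the pair rests on the pooled normal approximation, which is inferred from its agreement with the rest of the table; the position of n = 50 between n = 70 and n = 40 supports it independently. The power figures also assume exactly 50 and 1000 children and a true comparator cure of 90%.

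This is a correction worth making, because a wrong figure stands in a stated 80%-power scenario for a primary comparison and errs in the study's favour. It is not evidence of a fault in the design or the analysis.

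**What to change.** In Table 1, HIV infection or exposure, 5% prevalence, 90% comparator, replace 81.3 with 76.1 and leave the 13.9 as it is. The incomplete anemia entry (n = 100, 85% comparator) may be completed to 11.4 in the same pass as an optional tidy-up. The anemia value of 72.0 is rounding and needs no edit.

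The cost is one table cell. Sample size, endpoints and analysis are unchanged; the stated detectable cure percentage for this scenario simply becomes less favourable.
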